### Sample size {14}

The sample size is estimated by the change of BCVA using PASS 15.0 (PASS 15.0.5 NCSS, LLC, USA). According to a published paper [9], mean BCVA change of IVC from baseline to month 12 was 8.2 ± 9.5 ETDRS letters. The maximum difference of 5 ETDRS letters was chosen for non-inferiority margin between groups. The sample size was calculated based on α level of 0.05 and *β* level of 0.2, N1 = N2 = 46. Then, the ultimate sample size is 102 (51 of each group) assuming a 10% dropout rate.

The non-inferiority margin was chosen because 5 ETDRS letters is considered clinical insignificant in practice. And the sample size is also sufficient for analysis of the change of CST based on previous studies [9, 36] (364 ± 88.6 μm and 200 ± 210 μm for IVC and vitrectomy combined with ILM peeling respectively).

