### Trial design {8}

VVV is a single-center, prospective, parallel-group, non-inferiority, randomized controlled trial. Enrolled patients will be randomly assigned at a 1:1 ratio into the study group (PPV combined with ILM peeling) and control group (IVC), and a follow-up period of 12 months is planned. Interim analyses will not be conducted. Figure 1 depicts the trial design flow chart.

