### Statistical methods

#### Statistical methods for primary and secondary outcomes {20a}

Descriptive statistics will be used to summarize study results and demographic variables. Means and standard deviations will be used to describe the normally distributed data, and medians and interquartile ranges will be used for non-normally distributed data. Categorical variables will be described as percentage and frequency. The two-sample *t*-test or Kruskal–Wallis test will be used to assess continuous variables, while the chi-square test will be used to evaluate categorical variables. A two-sided *p* value of less than 0.05 will be considered statistical significance. Besides, the records of patients with missing data will be deleted to ensure the accuracy of the results. All the data will be analyzed by SPSS 25.0 (Chicago, IL, USA).

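### The 46 per group give 80% power only at one-sided 0.05; at the two-sided 0.05 level set for the analysis, power is about 70%

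*Protocol article*

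**What the plan says.** Trial design {8} declares the framework: "VVV is a single-center, prospective, parallel-group, non-inferiority, randomized controlled trial", with 1:1 allocation.

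Sample size {14} bases the calculation on change in BCVA. The inputs are:

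- from a published conbercept study, "mean BCVA change of IVC from baseline to month 12 was 8.2 ± 9.5 ETDRS letters";
- the margin: "The maximum difference of 5 ETDRS letters was chosen for non-inferiority margin between groups";
- the error rates: "The sample size was calculated based on α level of 0.05" and a β "level of 0.2, N1 = N2 = 46".

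After the allowance for loss, "the ultimate sample size is 102 (51 of each group) assuming a 10% dropout rate". The section does not say whether α is one- or two-sided.

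Statistical methods for primary and secondary outcomes {20a} sets the criterion for the analysis: "A two-sided *p* value of less than 0.05 will be considered statistical significance". No one-sided 5% level, no 90% confidence interval and no exception for the non-inferiority comparison appears anywhere in the article.

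**The concern.** A non-inferiority test is directional. A two-sided 0.05 criterion carried over to it means that the lower limit of a 95% confidence interval must lie above −5 letters, which is a one-sided 0.025 test. If the sample size was worked out at one-sided 0.05, sizing and analysis use different type I error rates, and the β of 0.2 does not belong to the test that will be done.

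Two things are at stake. First, if the treatments are truly equal, the chance of failing to show non-inferiority at the stated criterion is about 30% rather than 20%. Second, nothing in the article fixes which interval decides the result. Some results would pass on a 90% interval and fail on a 95% one, so a choice made after the data are seen could decide the conclusion on a primary outcome.

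**Working it through.** **Inputs from the article.** SD of BCVA change 9.5 letters, margin 5 letters, β 0.2 and 46 per group (Sample size {14}); 1:1 allocation (Trial design {8}); two-sided 0.05 and a two-sample t-test (Statistical methods {20a}).

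**Assumptions not in the article.** The true difference between groups is 0, and the SD is 9.5 in both groups. The article gives an SD of BCVA change for conbercept only.

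**Step 1: reproduce the 46.** The normal approximation is n = 2·SD²·(z₁₋α + z₁₋β)² / margin² per group.

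- One-sided 0.05: 2 × 9.5² × (1.645 + 0.842)² / 25 = 44.7, so 45.
- One-sided 0.025: 2 × 9.5² × (1.960 + 0.842)² / 25 = 56.7, so 57.

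The exact version uses the noncentral t distribution with 2n − 2 degrees of freedom and noncentrality 5 / (9.5·√(2/n)). At one-sided 0.05, 45 per group give 79.7% and 46 give 80.5%. So 46 is the smallest size that reaches 80%, which matches the stated figure and shows which level was used.

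**Step 2: power at the level set for the analysis.** With n = 46 the noncentrality is 5 / (9.5 × √(2/46)) = 2.524.

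| Evaluable per group | Power, one-sided 0.05 | Power, one-sided 0.025 |
|---|---|---|
| 45 | 79.7% | 69.5% |
| 46 | 80.5% | 70.4% |
| 51 (no loss) | 84.0% | 74.9% |
| 57 | 87.4% | 79.5% |
| 58 | 88.0% | 80.2% |

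The t-based size for 80% power at one-sided 0.025 is therefore 58 per group. Dividing by 0.90 for dropout gives 64.4, so 65 per group or 130 in total, against the planned 102.

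**Step 3: results on which the choice of interval matters.** With 46 per group the standard error is 9.5 × √(2/46) = 1.98 letters. The t quantiles on 90 degrees of freedom are 1.662 and 1.987, so the half-widths are 3.29 (90% interval) and 3.94 (95% interval). Non-inferiority needs an observed difference (surgery minus conbercept) above −5 + 3.29 = −1.71 letters on the 90% interval, or above −5 + 3.94 = −1.06 on the 95% interval. Any result between −1.71 and −1.06 passes one and fails the other.

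**Step 4: what baseline adjustment could recover.** ANCOVA on baseline BCVA reduces the residual SD to 9.5·√(1 − r²), where r is the correlation between baseline and change. The article gives no r, so a range is assumed. With 46 per group at one-sided 0.025:

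| Assumed r | Residual SD | Power |
|---|---|---|
| 0.3 | 9.06 | 74.5% |
| 0.4 | 8.71 | 77.8% |
| 0.5 | 8.23 | 82.2% |

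The 80% mark is crossed between r = 0.4 and r = 0.5.

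**The case against.** The best defence is that no sum is wrong. The 46 follows from the stated inputs once α is read as one-sided, which is a natural reading for a directional test and a level a trial may choose. On this view the two-sided rule in {20a} is a general statement about t-tests, Kruskal–Wallis and chi-square tests of difference. It mentions neither the margin nor an interval, and the analysis plan, which is not shown, may settle the matter. The 30% failure risk is also conditional: it needs one-sided 0.025 to govern and 46 evaluable per group. The missing-data statements in {20a} (deletion) and {20c} (imputation) point in different directions, so the number analysed could be as high as 51.

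Part of this stands. The calculation is sound for one-sided 0.05, so the fault is a mismatch between two sections rather than a slip in the formula. Whether the choice of interval is still open in the full plan cannot be known from the article.

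The rest does not remove the point. Section {20a} is headed as covering the primary outcome, contains no limit to tests of difference, and is the only place where a sidedness is given. If it was meant for difference tests alone, the non-inferiority comparison has no stated sidedness at all. Analysing all 51 per group raises power only to 74.9%. This is also not a detail left for later: the printed β and the printed criterion cannot both hold for the non-inferiority test.

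**Conclusion.** The concern holds. The sample size was worked out at one-sided 0.05, while the only criterion stated for the analysis is two-sided 0.05. At that criterion, power is 70.4% with 46 evaluable per group and 74.9% with all 51, against the planned 80%. Reaching 80% would take 58 evaluable per group.

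These figures assume a true difference of zero and an SD of 9.5 in both groups. If surgery were in truth slightly worse on BCVA, or its outcomes more variable, power would be lower at either level. If a one-sided 5% test was intended, the 46 is right, but the article has to say so and the rule in {20a} has to be narrowed.

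**What to change.** State one level and its matching interval in both Sample size {14} and Statistical methods {20a}, before any comparative data are examined. Either of two wordings would do.

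- **(a) 95% interval.** Non-inferiority is judged on the lower limit of the two-sided 95% confidence interval (one-sided α 0.025). With 46 evaluable per group, unadjusted power is about 70%. ANCOVA with baseline BCVA as covariate becomes the primary analysis; Methods for additional analyses {20b} already foresees regression adjustment. Any gain in power claimed for it should be labelled as resting on an assumed correlation.
- **(b) 90% interval.** Non-inferiority is judged at one-sided α 0.05, using the two-sided 90% confidence interval, with 80% power. The two-sided 0.05 rule in {20a} is then expressly limited to tests of difference.

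Both are changes of wording, and neither adds patients. Option (a) costs a less favourable stated power: 80% is regained only if the correlation lies above a value between 0.4 and 0.5. Option (b) keeps the 80% but openly accepts a one-sided type I error of 5%, twice that of a 95% interval.

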### Eligibility criteria {10}

The following are the criteria for the inclusion of candidates: (1) ≥ 18 years of age; (2) patients and their families fully understand the research and must sign an informed consent form; (3) diagnosed with type 1 or 2 diabetes mellitus; (4) hemoglobin A1c (HbA1c) levels of < 10% within 3 months; (5) moderate or severe nonproliferative diabetic retinopathy (NPDR) and proliferative diabetic retinopathy (PDR) without vitreous/preretinal hemorrhage [33]; (6) clear media for adequate OCT and OCTA images; (7) treatment-naïve DME diagnosed clinically; (8) CST of > 300 μm; (9) Early Treatment Diabetic Retinopathy Study (ETDRS) BCVA between 24 and 73 letters on the day of randomization; (10) treatment within 12 months of DME diagnosis; (11) no contraindication of vitrectomy or conbercept intravitreal injection. Each participant will only have one eye examined. If both eyes are qualified, the researcher will decide which of the eyes will be included in this study.

Exclusion criteria include the following: (1) any previous DME treatment (i.e., anti-VEGF injections, intravitreal corticosteroid usage, or macular photocoagulation); (2) macular edema caused by other diseases (i.e., age-related macular degeneration, retinal vein occlusion); (3) any previous intraocular surgeries (cataract surgery performed at least three months before study entry will not be exclusionary); (4) vision loss caused by other ocular diseases (i.e., glaucoma, high myopia); (5) a follow-up duration of < 12 months; (6) severe dysfunction of the heart, liver, kidney, lung, or other organs.

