### Explanation for the choice of comparators {6b}

The changes in CST and BCVA are the primary outcomes in this study. BCVA reflects the visual function of patients under the best-corrected refractive state, and it is widely used to evaluate the efficacy of clinical therapy. It is also a primary goal for patients seeking treatment. CST is an anatomical outcome that can reflect macular edema among patients.

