### Outcomes {12}

#### Primary outcome

The primary outcome is the changes in BCVA and CST from baseline to month 12 between the two groups.

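### CST is a primary outcome of a non-inferiority trial but has no margin, and the figures cited to call the sample size sufficient for it do not support non-inferiority

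*Protocol article*

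**What the plan says.** Trial design {8} fixes the framework: "VVV is a single-center, prospective, parallel-group, non-inferiority, randomized controlled trial". Two sections of the protocol article give BCVA and CST equal rank. Explanation for the choice of comparators {6b} states: "The changes in CST and BCVA are the primary outcomes in this study". The Primary outcome section states: "The primary outcome is the changes in BCVA and CST from baseline to month 12 between the two groups".

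Sample size {14} works from BCVA alone: "The sample size is estimated by the change of BCVA using PASS 15.0". The inputs are that "mean BCVA change of IVC from baseline to month 12 was 8.2 ± 9.5 ETDRS letters", a margin of 5 letters, α 0.05 and β 0.2, which give 46 per arm, or 102 in total after dropout. The only margin, and the only reason given for a margin, is in letters.

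The same section then adds that "the sample size is also sufficient for analysis of the change of CST based on previous studies" and supports this with "364 ± 88.6 μm and 200 ± 210 μm for IVC and vitrectomy combined with ILM peeling respectively". It gives no CST margin, hypothesis, power or number per arm.

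The statistical methods section {20a} offers a two-sample t-test or Kruskal–Wallis test for continuous variables, at two-sided 0.05. It does not distinguish the two primary outcomes.

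**The concern.** For a primary outcome of a non-inferiority trial, a sample size is sufficient only relative to a margin, and CST has none. The figures offered in its place, if they are changes as the sentence says, show the experimental arm doing worse by a wide distance. The statement then supports the opposite of the trial's aim.

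Two things are at stake. A reader will take it that the trial is adequately powered on both primary outcomes, which has not been shown for CST. And if BCVA turns out non-inferior while CST does not, or the reverse, the article gives no basis for saying whether the trial succeeded. Counting success on either outcome raises the false-positive rate; requiring both lowers the power.

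**Working it through.** **1. The plan's own figure (BCVA).** Inputs from Sample size {14}: SD 9.5, margin 5, power 80%; true difference taken as 0.

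n per arm = 2 × 9.5² × (z₁₋α + z₀.₈)² / 5²

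- One-sided 0.05: 2 × 90.25 × (1.645 + 0.842)² / 25 gives 45; the t-based version gives 46. The stated 46 reproduces.
- One-sided 0.025: the same formula gives 57, or 58 on the t-based version. It does not reproduce.

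So the BCVA calculation used one-sided 0.05. Both levels are carried below because the analysis section states two-sided 0.05.

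**2. CST figures read as changes.** Inputs from Sample size {14}: 364 (SD 88.6) for IVC, 200 (SD 210) for PPV, 46 per arm.

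- Difference: 364 − 200 = 164 μm less thinning with PPV.
- SE = √((88.6² + 210²)/46) = √(51,950/46) = 33.6 μm.
- z = 164/33.6 = 4.88; two-sided power at 0.05 is 99.8%. Sixteen per arm would already give 80%.
- Non-inferiority power at a margin of 100 μm, if PPV is truly 164 μm behind: Φ((100 − 164)/33.6 − 1.645) = Φ(−3.55) ≈ 0.02%. Smaller margins, or one-sided 0.025, give less.

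**3. Same SDs, true difference zero.** Smallest margin with 80% power at 46 per arm:

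- One-sided 0.05: (1.645 + 0.842) × 33.6 ≈ 84 μm.
- One-sided 0.025: (1.960 + 0.842) × 33.6 ≈ 94 μm.

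The documents state no CST margin, so a range of assumed margins is shown. The 50 μm row matches a CST change used in the re-treatment criteria under Further intervention; it is an illustration, not a proposed margin.

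| Assumed margin | n per arm, one-sided 0.05 | n per arm, one-sided 0.025 |
|---|---|---|
| 25 μm | 514 | 653 |
| 50 μm | 129 | 164 |
| 75 μm | 58 | 73 |
| 100 μm | 33 | 41 |

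At 50 μm, 46 per arm gives about 44% or 32% power. The answer depends heavily on the SDs: for 50 μm, an SD of 88.6 in both arms needs 39 or 50 per arm, and 210 in both needs 219 or 277.

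**4. Other readings of 364 and 200.**

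- *364 a level, 200 a change:* the difference of 164 has no meaning and no power statement follows.
- *Both end levels:* PPV would be 164 μm better. But the sentence says change, and a thickness of 200 ± 210 μm puts Φ(−200/210) ≈ 17% of eyes below zero under a normal model.

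**5. Two primary outcomes.** If either could carry success and the tests were independent, the false-positive rate would be 1 − 0.95² = 9.75% at one-sided 0.05 each, or 1 − 0.975² = 4.9% at one-sided 0.025 each. The bounds without independence are 10% and 5%. If both are required, joint power cannot exceed the roughly 80% planned for BCVA. If CST also had 80% and the outcomes were independent, it would be 0.8 × 0.8 = 64%.

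**The case against.** The strongest reply is that the sentence claims only enough patients for an analysis of CST change, not for CST non-inferiority. The only CST test in the article is an ordinary two-sample comparison, and for that 46 per arm is ample. This stands: a reader might infer that the claim fails on every reading, and it does not. It holds for a plain difference test, though in the stated order that difference goes against PPV. What it does not do is support the non-inferiority aim that the design declares.

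A reader might also conclude that 364 must be a level. The tempting argument is that a mean fall of 364 μm to 250 μm would need a mean baseline of 614 μm, while entry requires only "CST of > 300 μm". But the 250 μm in the background section belongs to a definition of refractory disease, not to an expected month-12 mean, and the entry criterion is a floor that says nothing about the mean baseline. The documents give no baseline or final CST for the cited studies, so this remains a query.

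Two ways of stating the size should be avoided. Expressing 84–94 μm as a share of the 200 μm PPV figure uses the wrong arm, because a margin is judged against the comparator's effect, and it is uncertain whether 364 is such an effect. Quoting a false-positive rate near 10% without its condition is also too strong, since under the analysis section's two-sided 0.05 it is about 5%.

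Finally, a both-or-either rule may properly sit in a statistical analysis plan that is not shown, so its absence alone would not be an error. The sufficiency claim, however, is made in this document. The BCVA calculation is not affected.

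**Conclusion.** The point holds in this form: CST is declared primary in a non-inferiority trial without a margin, and the cited figures do not support the statement that the sample size suffices for it. Taken literally as changes, they put PPV 164 μm behind, with 99.8% power to show it worse and under 0.1% power for non-inferiority at margins up to 100 μm. With no true difference, the design reaches 80% power only at margins of about 84 to 94 μm. The one reading that would favour PPV, both figures as end levels, conflicts with the sentence's own wording and with an SD larger than the mean.

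These results assume 46 evaluable patients per arm, the cited SDs and a normal approximation. With all 51 per arm evaluable, the margins fall only to about 79 and 89 μm. The documents cannot show whether the two figures are the same quantity.

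**What to change.** Check both CST figures against the cited studies. Then delete the sufficiency sentence, or replace it with mean change and SD of change in each arm and the confidence-interval half-width that the sample size gives. With the present SDs that half-width would be 1.96 × 33.6 ≈ 66 μm for a 95% interval.

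Before recruitment (the Trial status section says it had not begun), choose one of two structures:

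- *Preferred:* month-12 BCVA change as the sole primary outcome, non-inferiority at 5 letters. CST change becomes the first key secondary, reported as a baseline-adjusted difference (ANCOVA) with confidence interval, and tested only after BCVA non-inferiority is shown.
- *Alternative:* keep CST co-primary, state that both must succeed, give and justify a CST margin, and restate the joint power.

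The preferred option costs CST its co-primary status. It needs a protocol amendment with ethics approval, as the section on communicating amendments {25} requires, and a registry update, but no extra patients or measurements. The alternative may need more patients, depending on the margin, as the table in the working shows.

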### Recruitment {15}

We will promote the study through various channels, including outpatient clinics, social media, and internal hospital announcements, to reach a wide audience. We will regularly assess the progress of participant recruitment and make necessary adjustments to the recruitment strategies to ensure the smooth conduct of the study.

### Assignment of interventions: allocation

#### Sequence generation {16a}

One hundred and two random numbers will be generated by computer-generated algorithm (SPSS software), and the corresponding participants will be evenly distributed to the study group (the first 51 numbers) and the control group (the last 51 numbers) according to the random number sequence.

#### Concealment mechanism {16b}

The allocation sequence will be concealed for both investigators and participants by opaque envelopes. Once patients are enrolled and have signed the informed consent form, they will receive the corresponding intervention based on the group assigned in the envelope.

#### Implementation {16c}

The allocation sequence will be generated by a designated investigator, and the assignment of participants to interventions will be carried out by the same person. Participant enrollment will be conducted by the principal investigator.

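### One investigator both generates the allocation sequence and assigns participants, which contradicts the statement that the sequence is concealed from investigators

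*Protocol article*

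**What the plan says.** Four places in the protocol article bear on this.

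- **Sequence generation {16a}:** 102 computer-generated random numbers are used. The split is given as "evenly distributed to the study group (the first 51 numbers) and the control group (the last 51 numbers) according to the random number sequence", and the section says no more about it.
- **Concealment mechanism {16b}:** on who is kept from the list, it states: "The allocation sequence will be concealed for both investigators and participants by opaque envelopes". On timing, the envelope determines treatment only after enrolment and consent.
- **Implementation {16c}:** a designated investigator produces the list, while "the assignment of participants to interventions will be carried out by the same person". The section ends: "Participant enrollment will be conducted by the principal investigator".
- **Eligibility criteria {10}:** one eye per participant is studied. If both qualify, "the researcher will decide which of the eyes will be included in this study".

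For context, the trial is single-centre (Trial design {8}). Participants and surgeons are not masked (section {17b}). Outcome assessors and data analysts are masked (section {17a}).

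**The concern.** Concealment is meant to ensure that whoever decides if, when and with which eye a patient enters does not know the next allocation. Opaque envelopes achieve this only against people who have not seen the list. Here the person who made the list also carries out assignment.

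If that person can influence entry, or inform those who decide on it, patients or eyes could be matched to arms. The eligibility criteria leave some room for judgement: absence of contraindications to either treatment, severe organ dysfunction, and the choice of eye. Masked assessment protects how visual acuity and OCT are measured, but not who ends up in which arm. The regression adjustment in section {20b} can correct imbalance only in factors that were measured. Selection bias cannot be repaired once patients are in.

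**Working it through.** The core of the check is a reading of the sections against each other. A short calculation then shows where the exposure lies.

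**1. The contradiction.** Section {16b} says the sequence is concealed from investigators, without exception. Section {16c} says the sequence is made by an investigator, who then assigns. Someone who has generated a list can know it, so {16b} is false for at least that one investigator.

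**2. Is the gap closed elsewhere?** Section {16c} gives enrolment to the principal investigator. For this to protect entry decisions, two things must hold:

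- the designated investigator is not the principal investigator;
- the list is not available to whoever enrols.

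The article states neither. Sections {9} and {26a} also describe a dedicated investigator who talks to eligible patients, and delegated sub-investigators who inform candidates before consent. Nothing bars the designated investigator from these tasks.

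**3. Order of events.** Section {16b} places the intervention after enrolment and consent. Table 1 places screening, visual acuity and OCT before allocation. The article does not say that the choice of eye is recorded before the envelope is opened.

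**4. How predictable is the list, and to whom?** The only figure is the list length: 51 + 51 = 102, in line with Sample size {14}. Assume the list is in random order. For a balanced list of 2m allocations, someone who sees only past allocations and always guesses the arm with more places left expects this many correct guesses:

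m + (4^m / C(2m, m) − 1) / 2

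The expected number of allocations already certain at the end of the list is 2m / (m + 1). Blocks of 4 and 6 are shown for comparison only and are not in the protocol.

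| List | Expected correct guesses | Share correct | Share certain |
|---|---|---|---|
| One list, m = 51 | 56.8 of 102 | 55.7% | 102/52 = 1.96 of 102 |
| Known blocks of 4, m = 2 | 2 + (16/6 − 1)/2 = 2.83 of 4 | 70.8% | (4/3)/4 = 33% |
| Known blocks of 6, m = 3 | 3 + (64/20 − 1)/2 = 4.1 of 6 | 68.3% | (6/4)/6 = 25% |
| Any list, to the person who holds it | 102 of 102 | 100% | all |

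A simulation of 20,000 lists with m = 51 gave 56.84 correct guesses and 1.96 certain allocations. The exposure therefore comes from who holds the list. The lack of blocks is not its source.

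**5. The wording of {16a}.** There are two readings of "the study group (the first 51 numbers) and the control group (the last 51 numbers". If the 102 numbers are ranked and arms follow rank, this is a valid random allocation rule. If first and last mean order of entry, every allocation is known in advance and arm coincides with calendar time. No ranking step is stated.

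**The case against.** The strongest reply is that concealment mainly protects the decision to enrol. That decision belongs to the principal investigator, and the envelope comes into play only after enrolment and consent. If the two roles are held by different people and the list is not shared, the enroller does not know what comes next. This stands, and it limits the finding: the text leaves concealment unsecured but does not show that it fails. It does not remove the contradiction between {16b} and {16c}.

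On the study eye, the reply is that eligibility is checked eye by eye before allocation in Table 1, so the choice is probably made by then. That is fair as to the likely order. An explicit statement is still worth adding, because the choice is discretionary.

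A reader might infer three stronger things that the documents do not support:

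- **Missing blocks are part of the fault.** The table shows the opposite for guessing from past allocations: 55.7% for one list against 70.8% for known blocks of 4. A condensed article's silence on blocks is also weak evidence that there are none.
- **Arms are filled in order of entry.** The words after the 51/51 split tie the distribution to the random number sequence, and envelopes would be pointless otherwise. The ranked reading is the more natural one, so the wording needs clarifying but is not shown to be wrong.
- **Open-label status breaks concealment.** It does not. It only gives foreknowledge more room to matter.

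**Conclusion.** The point holds as a contradiction in a stated arrangement: one investigator can know all 102 allocations, while the article says investigators are kept from the sequence. It should be corrected before recruitment.

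To go further and say that concealment is defeated would need evidence that the list-holder enrols patients or shares the list, and the article is silent on both. Nor can a bias in letters be given against the 5-letter margin. The documents contain nothing on how often entry might be steered or how far prognosis would differ, and the primary outcome is change from baseline, so a better-seeing eye need not gain more.

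The conclusion rests on reading {16c} as written, with generator and assigner being the same individual. The predictability figures also assume the ranked reading of {16a}.

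**What to change.** 1. **Implementation {16c}:** delete the same-person wording. State that the sequence is generated, and the opaque envelopes prepared and held, by someone with no role in enrolment or assignment, for example an existing team member not involved in recruitment. That person hands over the next sealed envelope and takes no part in deciding who enters. State also that the principal investigator and anyone else who recruits has no access to the list.
2. **Concealment mechanism {16b}:** state that each allocation is released only after eligibility, baseline visual acuity and OCT, and the chosen study eye have been recorded.
3. **Sequence generation {16a}:** state that the 102 random numbers are ranked and the arms assigned by rank, so that the 51/51 split cannot be read as order of entry.

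Permuted blocks and a fixed rule for choosing the eye are design preferences and are not needed to resolve this point. An electronic randomisation module is not needed either. Data management {19} describes the data-capture system for data entry only, so one should not be assumed to exist.

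The cost is a small reassignment of duties and some rewording. Trial status says recruitment has not started, so both can be done before the first patient.
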